| **Statistical methods** | A descriptive statistical analysis is made on the proportion of patients with good prognosis (mRS=0-2 points) and the proportion of patients with poor prognosis (mRS=3-5 points) and death (mRS=6 points) at 90 days after treatment, the corresponding number of cases and the proportion are calculated, and χ^2^ or Fisher's exact test is adopted to compare the inter-group difference. If the inter-group difference is of statistical significance, the Bonferroni method is adopted to adjust the size of test α value, and inter-group pairwise comparison is further made.  The changes in National Institutes of Health Stroke Scale (NIHSS) and EQ 5 visual analogue scale (EQ-5D) at discharge from baseline: if the score difference between before treatment and after treatment is in normal distribution and satisfied homoscedasticity, then analysis of variance is performed. If the statistical test results of the analysis of variance are of statistical significance, statistical analysis is further performed, and the Bonferroni test is carried out for pairwise comparison. Otherwise, the Kruskal Wallis method is adopted to perform statistical test. If the statistical test results of the Kruskal Wallis are of statistical significance, statistical analysis is further performed, and the Wilcoxon rank test is carried out, and the Bonferroni method is adopted to correct P value for pairwise comparison.  The descriptive statistical method is adopted to perform the analysis on all the data. As for the measurement data, number of cases (missing number), mean value, median, standard deviation, first quartile, third quartile, maximum and minimum are described, and the 95% confidence interval of the mean is calculated; as for the enumeration data, the frequency is described. It the hypothesis test needs to be carried out, the corresponding hypothesis test methods are adopted according to the nature of materials and the purpose of the test.  Unless otherwise specified, the hypothesis test adopted by this study is two-sided test with 0.05 as the size of test. P value ≤ 0.05 meant that the difference is of statistical significance.  Based on whether the score difference before and after treatment is in normal distribution, the paired t-test is adopted to make an inter-group comparison on measurement data, or the Wilcoxon signed rank test is used for analysis; χ ^2^ test or Fisher exact probability test is adopted to analyze the enumeration data; the Wilcoxon rank test is adopted to analyze the ranked data. |

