The results of internal investigation of our company indicated that, the domestic therapeutic regimen for AIS was mainly combined medications; the proportion of the patients that received three-drug regimen and four-drug regimen was relatively high: for example, the proportion of patients that used Chinese herbal medicine + antiplatelet drug + cerebral circulation improving drug was 40%, and the proportion of the patients that used Chinese herbal medicine + antiplatelet drug + cerebral circulation improving drug + nerve protective agents was 87%. One meta analysis[[8]](#bookmark9) included 145 RCT studies, where the data on the efficacy and safety of a total of 13289 Chinese Patients were collected, the main outcome index was NIHSS score and clinical effectiveness rate, and the results indicated that the efficacy of Edaravone + Kininogenase was superior to that of Sodium ozagrel; Edaravone+ Kininogenase, as well as the Sodium ozagrel + Edaravone are the most efficacious therapeutic regimen, and can improve the nerve functional disorder. The systematic evaluation on Chinese herbal medicine ligustrazine in treating acute ischemic cerebral stroke[[9]](#bookmark10) indicates that, the combination of ligustrazine with conventional therapies can better lower the score of nerve functional defects than the conventional therapies (*MD*=2.49, 95%CI: 1.00, 3.98). There is no clear conclusion on whether which combined drug regimen is the most efficacious on the patients who miss the timing of thrombolysis.

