**2 Study objective**

Primary study objective:

Analysis of current treatment situation in acute phase of acute ischemic stroke in real-world settings。

Secondary study objectives

(1) Comparison of effects of various drug combinations in treatment of acute ischemic stroke in real-world settings.

(2) Analysis of cost-utility of various drug combinations in treatment of acute ischemic stroke.

(3) Analysis of occurrences of complications and adverse events during treatment in hospital in patients with acute ischemic stroke.

(4) Analysis of effects of TOAST typing on specific therapy regimens in acute phase of acute ischemic stroke.

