# 5 Treatment regimen

In the study, the doctors can select the specific treatment regimen for cerebral stroke according to the patient's clinical medical history and characteristics of symptoms as well as the China 2011 Guidelines for Diagnosis and Treatment of Ischemic Cerebral Stroke. This study has no limitations on the selection, dose and treatment course of the treatment drugs.

According toChinese Guideline for Diagnosis and Management of Acute Ischemic Stroke2010, The specific treatment on acute ischemic cerebral stroke refers to the intervention with a certain link in the pathophysiological mechanism of ischemic injuries. Examples are given to the following common drugs for illustration:

1. Intravenous thrombolysis drug: rt-PA and urokinase.
2. Anti-platelet drugs: aspirin and Clopidogrel
3. Anticoagulants: including unfractionated heparin, low molecular heparin, ateroid, oral decoagulants and thrombin inhibitor.
4. Volume expansion drug: hydroxyethyl starch, and low molecular dextran.
5. Nerve protective agents: Edaravone, nicholin and ganglioside.
6. Cerebral blood flow perfusion improving drugs: butylphthalide, human urine kininogenase (Urinary Kallidinogenase for Injection).
7. Chinese herbal medicines: Shuxuetong injection, and Danhong injection.

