**10.1 Determination of sample size**

For a more comprehensive collection of the patient information on the use of various drug combinations, this study protocol is planned to include 10,000 patients with acute stroke.

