**10.3 Analysis of efficacy**

FAS analysis is to be conducted for the efficacy indexes.

A descriptive statistical analysis is made on the proportion of patients with good prognosis (mRS=0-2 points) and the proportion of patients with poor prognosis (mRS=3-5 points) and death (mRS=6 points) at 90 days after treatment, the corresponding number of cases and the proportion are calculated, and χ^2^ or Fisher's exact test is adopted to compare the inter-group difference. If the inter-group difference is of statistical significance, the Bonferroni method is adopted to adjust the size of test α value, and inter-group pairwise comparison is further made.

The changes in National Institutes of Health Stroke Scale (NIHSS) and EQ 5 visual analogue scale (EQ-5D) at discharge from baseline: if the score difference between before treatment and after treatment is in normal distribution and satisfied homoscedasticity, then analysis of variance is performed. If the statistical test results of the analysis of variance are of statistical significance, statistical analysis is further performed, and the Bonferroni test is carried out for pairwise comparison. Otherwise, the Kruskal Wallis method is adopted to perform statistical test. If the statistical test results of the Kruskal Wallis are of statistical significance, statistical analysis is further performed, and the Wilcoxon rank test is carried out, and the Bonferroni method is adopted to correct P value for pairwise comparison.

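### All-pairs single-step Bonferroni is fixed with no bound on the number of regimen groups, so power per pair falls quickly as groups are added; Holm's step-down is a free but modest improvement

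*Protocol*

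**What the plan says.** The regimen comparison is secondary objective (1) in Protocol section 2: "Comparison of effects of various drug combinations in treatment of acute ischemic stroke in real-world settings". The primary objective is descriptive.

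Section 10.3 fixes how groups are compared. For good outcome (mRS 0–2), poor outcome and death at 90 days, a chi-square or Fisher test is run across groups. If it is significant, "the Bonferroni method is adopted to adjust the size of test α value, and inter-group pairwise comparison is further made". Changes in NIHSS and EQ-5D follow the same pattern, with analysis of variance or Kruskal-Wallis first and Bonferroni-corrected pairs after. The statistical methods in the abstract repeat this, and section 10.6 applies it to recurrence and dementia. The overall level is also in the abstract: "the hypothesis test adopted by this study is two-sided test with 0.05 as the size of test".

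On what the groups could be, section 5 states: "This study has no limitations on the selection, dose and treatment course of the treatment drugs". It names seven drug classes, introduced by "Examples are given to the following common drugs for illustration". On size, section 10.1 says that "this study protocol is planned to include 10,000 patients with acute stroke", and the reason given is descriptive: "For a more comprehensive collection of the patient information on the use of various drug combinations".

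**The concern.** With g groups there are g(g−1)/2 pairs. Single-step Bonferroni divides 0.05 by that number, so the threshold tightens roughly with the square of g, while the patients per group shrink in proportion to g. The protocol fixes the rule that drives this and leaves g open. Whether secondary objective (1) can be answered for an ordinary pair of regimens then depends on a count that the protocol does not limit. The same rule governs the primary efficacy endpoint (mRS 0–2) when it is compared between regimens.

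Single-step Bonferroni is also never more powerful than Holm's step-down procedure, which gives the same familywise guarantee under the same conditions. The stated method therefore gives up some power without gaining any error control.

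**Working it through.** **The protocol's own figure.** The 10,000 cannot be reproduced, because section 10.1 gives no effect size, outcome rate, power or number of groups.

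**Inputs.** From the protocol: N = 10,000, two-sided 0.05, Bonferroni over all pairs, seven example classes. Assumed, because the protocol states no rates: good outcome 60% against 70% unless noted, and equal groups.

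**Formula.** With m = g(g−1)/2, alpha = 0.05/m, n = 10,000/g, p̄ = 0.65:

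power = Φ{ [ |p₁−p₂|√n − z₁₋ₐ/₂·√(2p̄(1−p̄)) ] / √(p₁(1−p₁)+p₂(1−p₂)) }

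Here √(2×0.65×0.35) = 0.6745 and √(0.24+0.21) = 0.6708. For ten groups: (0.1×√1000 − 3.261×0.6745)/0.6708 = (3.162 − 2.199)/0.6708 = 1.435, and Φ(1.435) = 92%.

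| Groups | Pairs | Alpha per pair | n per group | Power, 60% v 70% | Power, 60% v 65% |
|---|---|---|---|---|---|
| 5 | 10 | 0.005 | 2,000 | >99% | 68% |
| 10 | 45 | 0.0011 | 1,000 | 92% | 17% |
| 20 | 190 | 0.00026 | 500 | 37% | 2% |
| 30 | 435 | 0.00011 | 333 | 12% | 0.6% |

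These figures ignore the overall test that must be passed first, which can only lower them.

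**Illustrative extreme.** Suppose every non-empty combination of the seven classes were a group.
- Groups: 2⁷ − 1 = 127. Pairs: 127×126/2 = 8,001. Alpha: 0.05/8,001 = 0.00000625, z = 4.518.
- Patients per group: 10,000/127 ≈ 79.
- Power for 60% v 70%: (0.1×√79 − 4.518×0.6745)/0.6708 = −3.22, so 0.06%. Across 50% v 60%, 60% v 70% and 70% v 80% it is 0.05% to 0.10%.
- At an unadjusted 0.05 the same three pairs have only 24% to 30%. Much of the loss is therefore sparsity and not multiplicity.

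**Large regimens at that same alpha, 60% v 70%.** 4,000 v 2,000 patients: above 99%. 2,000 v 1,000: 81%. 1,000 v 1,000: 57%.

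**What Holm adds.** I simulated 10,000 patients in equal groups, with assumed true rates evenly spaced from 58% to 66%, and took the average share of pairs rejected.
- 5 groups: Bonferroni 42%, Holm 46%.
- 10 groups: 10.4% and 10.9%.
- 20 groups: 1.2% for both.

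The gain depends on how far the rates differ. With ten groups spaced from 55% to 70% it is 39% against 41%.

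**The case against.** The strongest reply is that the protocol never says how many groups there will be. Section 5 lists the seven classes only as examples, and defining regimens, merging rare ones and setting a minimum group size are commonly left to a statistical analysis plan, which is not shown here. That stands: the missing group definition is not the finding. A reader might infer from section 5 that 8,001 tests are planned, but nothing in the protocol says so. Nor is 8,001 a ceiling, since grouping by individual drug would give more.

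A reader might also infer that the regimen comparison cannot succeed. The documents do not support this. With ten or fewer equal groups power is at least 92% for a 10-point difference, and large regimens keep useful power even at 0.000006. The introduction points to concentrated use: it reports from an internal survey that "the proportion of patients that used Chinese herbal medicine + antiplatelet drug + cerebral circulation improving drug was 40" per cent, and 87% for the four-class version. Those shares sum to 127%, so they cannot belong to exclusive regimens; nor can they be nested, since the four-class share would exceed the three-class share containing it. They support concentration only qualitatively.

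It is likewise tempting to say that groups would be chosen after outcomes are seen. No section says that.

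Finally, Bonferroni after an overall test is valid and controls error, so Holm improves it and does not correct an error. That also stands. It bears on how much weight the point carries, not on whether the change is worth making.

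**Conclusion.** The point holds in a limited form. The protocol fixes all-pairs single-step Bonferroni and sets no bound on the number of groups. Under equal groups and an assumed 60% against 70%, power per pair drops from 92% at 10 groups to 37% at 20 and 12% at 30; for 5 points it is low from 10 groups on. The 8,001-pair case shows only how far the rule can be stretched.

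The one change that follows from the protocol's own text is the choice of procedure. Holm dominates the stated method, but the gain is modest and fades where power is worst: it does not rescue a 20- or 30-group analysis. The rates, the equal split and the simulated spread of rates are assumptions.

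**What to change.** In the statistical methods of the abstract and in sections 10.3 and 10.6, replace single-step Bonferroni with Holm's step-down procedure for the pairwise comparisons: order the m p-values, compare the smallest with 0.05/m, the next with 0.05/(m−1), and so on, stopping at the first that fails. This changes wording only. The cost is that simultaneous confidence intervals are less direct under Holm than under Bonferroni.

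Optionally, state that the compared regimens will be fixed by frequency of use before any outcome data are seen, with rarer combinations described but not tested. This is what limits the number of groups. A minimum share of 5% of patients allows at most 100/5 = 20 exclusive regimens, and 10% at most 10. The cost is that rare combinations receive no test. It can equally be placed in the statistical analysis plan.

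Comparing each regimen with one reference would give more power (62% against 37% at 20 groups, same assumptions), but it answers a narrower question than secondary objective (1), which names no reference. That is a trade-off for the study team and not part of this fix.

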# 3 Overview of study design

This was a registered, prospective, multi-center clinical study. The study was planned to included 10, 000 patients with acute ischemic stroke (AIS) and record treatment regimens, treatment outcomes and medical expenses during hospitalization in real clinical practice. This study was to collect patients' data through a electronic data capture system (EDC).

According to the recommendations for treatment and follow-up observations in acute phase in the "Guidelines on diagnosis and treatment of acute ischemic stroke in China 2014 (Draft)", the patients with stroke were planed to receive 5 visits, which occurred at admission (baseline assessment, visit 1), 7 days ± 2 days after medication (visit 2), at discharge (visit 3), 90 days ± 14 days after medication (visit 4, outpatient service or telephone follow-up), and 360 days ± 28 days after medication (visits 5, telephone follow-up), respectively. As for the specifics, refer to [Study Flow Chart](#bookmark14).

In the baseline phase, the investigators should verify the inclusion/exclusion criteria, obtain the patients' informed consent, and try to collect the demographic information, past history, onset and admission conditions, and vital signs of the patients; and collect the following data of clinical examination: ECG, laboratory tests (blood routine, blood glucose, blood lipids, hepatic and renal functions, cardiac enzymes, serum electrolytes, coagulation) and imaging findings, and assess Glasgow Coma Scale, NIHSS score, mRS score and EQ-5D Scale. Seven days ± 2 days after medication, the vital signs of the patients were recorded and the NIHSS scores were accessed again. At discharge, the treatment regimen, vital signs, ECG and above laboratory tests results were recorded during hospitalization, and the Glasgow Coma Scale, NIHSS score, mRS score and EQ-5D scale were accessed, and the medical expenses during hospitalization was also collected. On 90 ± 14 days after medication, the recurrence of stroke, survival conditions and re-admissions were collected; the medical expense until this visits since discharge was recorded; and the mRS score, EQ-5D scale and MMSE scale (only applicable for the patients visiting the hospital) were accessed. On 360 days ± 28 days after medication, another telephone follow-up was given again, to ask the patient's health status, access mRS score, EQ-5D scale, and collect medical expenses.

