**7.3 Follow-up period**

**Visit 4(After administration 90 ± 14 days, Outpatient or telephone visit)**

- mRS score
- MMSE scale (Only applicable to the patients that receive follow-up visits at hospitals)
- EQ-5D scale
- Collect medical expenses

The patient's medical expenses from discharge to visit 4 are collected (AIS related medical expense, not including the medical expenses for other diseases), including direct medical cost (including the dug expense, examination expense, laboratory test expense, diagnosis and treatment expense, nursing expense and bed expense due to outpatient service / emergency service / hospitalization) as well as direct non-medical cost (including transportation expense, nutrition expense, family accompanying expense and the expense of auxiliary devices). The above expenses are obtained through the inquiry from the patient and (or) family. Where the expense list cannot be provided, the estimate value verbally given prevails.

- Recurrence

The patient should be inquired about the recurrence, and the date of recurrence and whether the recurrence leads to inpatient treatment should be recorded.

Note: whether the disease recurs is based on the diagnosis of the medical institution verbally told by the patient or his/her cerebral infarction.

The stroke recurrence is defined as: 1) in conformity with the diagnosis criteria of ischemic cerebral stroke; 2) the history of past stroke with clear symptom; 3) infarction foci at different periods verified by cranial CT/MRI[[13]](#bookmark15).

- Survival status

The patients should be inquired about the survival status, and as for the dead patients, it is necessary to record the date and reason of death.

- Re-admission

The patient should be asked whether he/she is re-admitted as well as the frequency and reasons of admission.

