**8.3 Pharmacoeconomic evaluation**

Calculate the cost/utility of the protocol of combinations of different drugs, and ascertain the optimal protocol of hospital treatment of patients with acute cerebral stroke. As for the costs, only the direct cost is collected, and the indirect cost and implicit cost are not collected. The direct costs in the study include:

- Direct medical cost (including the dug expense, examination expense, laboratory test expense, diagnosis and treatment expense, nursing expense and bed expense)

Discharge visit (Visit 3): Collect the direct medical cost according to the fees list of patients on discharge.

Visit 4 and visit 5: collect the direct medical costs by inquiring the patients or their families.

- Direct non-medical cost (including transportation expense, nutrition expense, family accompanying expense)

Directly collect the transportation costs and the nutrition costing by inquiring the patients or their families, and collect the nursing fees of the families by inquiring the families of the days/hours of downtime and calculating the fees through multiplying the days/hours by the local average wage.

In the utility analysis, quality-adjusted life years (QALYs) are used as the index of health outcome. The cost unit is Renminbi (RMB).

The QALY values are calculated through the utility value acquired by EQ-ED (evaluated on day 0 before treatment, at discharge,on 90 ± 14 days after treatment, 360 ± 28 days after treatment), and the pathway of the quality of life can be acquired by connecting the utility values on day 0, at discharge, on 90 ± 14 days after medication. With the time required for improving the quality of life as weights, we will get the QALY values. See the reference for the calculation method. [[14]](#bookmark16)

The EuroQol-5 Dimensions (EQ-5D) consists of two parts: the questionnaire and the conversion table of utility values. The questionnaires results can be used to describe the health status of the population and access to the EQ-VAS scores, and the EQ-5D index score can be further acquired by using the the time trade off (TTO) conversion table of utility values. Given that there is no suitable TTO conversion table of utility values in Chinese, the conversion table of utility values for Japanese is used to acquire the EQ-5D index scores. The following is the TTO conversion table of utility values in Japanese [[15]](#bookmark17):

| **Dimensions of EQ-5D** | **Level** | **Index** |
| --- | --- | --- |

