**10 Statistical methods**

The descriptive statistical method is adopted to perform the analysis on all the data. As for the measurement data, number of cases (missing number), mean value, median, standard deviation, first quartile, third quartile, maximum and minimum are described, and calculate the 95% confidence interval of the rates. Based on whether the score difference before and after treatment is in normal distribution, the paired t-test is adopted to make an inter-group comparison on measurement data, or the Wilcoxon signed rank test is used for analysis; χ ^2^ test or Fisher exact probability test is adopted to analyze the enumeration data; the Wilcoxon rank test is adopted to analyze the ranked data.

If needed, the missing data of visits in efficacy analysis will be filled in using last observation carried forward (LOCF) method.

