**10.2 Analysis Data Sets**

All subjects who receive at least 1 dose of investigational drug and have at least 1 efficacy evaluation data after baseline are included in FAS, according to the basic principle of intention-to-treat (ITT) analysis.

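### Last observation carried forward has no exception for death, so an in-hospital death can outrank a worsening survivor on change to discharge in NIHSS and EQ-5D VAS

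*Protocol*

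**What the plan says.** Two of the three secondary efficacy endpoints in protocol section 8.1 are changes from baseline to discharge. Section 10.3 analyses "The changes in National Institutes of Health Stroke Scale (NIHSS) and EQ 5 visual analogue scale (EQ-5D) at discharge from baseline" by analysis of variance if normality and equal variance hold, otherwise by Kruskal-Wallis, with Bonferroni-corrected pairwise tests after a significant result.

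Four other statements decide what happens to a patient who dies before discharge:

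- Section 10, on missing scores: "If needed, the missing data of visits in efficacy analysis will be filled in using last observation carried forward (LOCF) method". Death is not excepted.
- Section 10.2, on the full analysis set: besides at least one dose, patients must "have at least 1 efficacy evaluation data after baseline are included in FAS".
- Section 3, on the only assessment between baseline and discharge, at day 7 ± 2: "the vital signs of the patients were recorded and the NIHSS scores were accessed again". The study flow diagram agrees and shows no EQ-5D at that visit.
- Section 8.3, on the EQ-5D time points: "evaluated on day 0 before treatment, at discharge,on 90 ± 14 days after treatment, 360 ± 28 days after treatment".

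Death has a value only on the mRS (6, Annex 2). Section 7.3 requires that "as for the dead patients, it is necessary to record the date and reason of death". Section 9.2 asks for a final evaluation on leaving the study, except after loss to follow-up, and does not mention death.

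**The concern.** A discharge NIHSS or VAS that is absent because the patient died is not missing in the usual sense: the outcome is known, and it is the worst one possible. Carrying forward a score taken while the patient was alive treats it as no change or a modest change. Leaving the patient out restricts the comparison to those who survived treatment.

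Comparing the effects of drug combinations is the first secondary objective (section 2). Physicians choose regimens without restriction (section 5). The listed drugs include thrombolytics and anticoagulants, and the flow diagram singles out symptomatic haemorrhagic transformation for special attention. Unequal in-hospital mortality between regimens is therefore plausible. If it occurs, these two endpoints would largely or wholly fail to show it.

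**Working it through.** **Tracing the rules through the visit schedule**

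| Time of in-hospital death | VAS, carried forward | NIHSS, carried forward | No carrying forward |
|---|---|---|---|
| After Visit 2 (day 7 ± 2) | Baseline carried: change 0 | Visit 2 score carried: change while alive | Not in the comparison |
| Before Visit 2 | Change 0, or patient outside the full analysis set | Change 0, or patient outside the full analysis set | Not in the comparison |

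The VAS entry is exactly 0 because day 0 is the only earlier EQ-5D. Section 10 does not limit carrying forward to post-baseline values. If it were so limited, VAS would fall into the last column.

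**Ordering.** This step needs no assumed rate. A carried change of 0 ranks better than a survivor's rise of 1 NIHSS point, and better than any fall in a survivor's VAS. A patient who had improved by Visit 2 and then died is counted as improved on NIHSS.

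**Size.** The protocol gives no mortality rate, score change or SD, and the 10,000 patients in section 10.1 rest on no effect size, so there is no planned figure to reproduce. What follows is an illustration.

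Let d be a regimen's in-hospital mortality, s the mean change in survivors (the same in both regimens) and x the change given to a death. The mean is (1 − d)s + dx, so the difference B − A is (dB − dA)(x − s).

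Assumed: s = +15 for VAS and −3 for NIHSS. Carried forward, x = 0. For contrast, death is given a poor score: x = −50 for VAS, x = +30 for NIHSS. The multipliers (x − s) are then:

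- VAS: 0 − 15 = −15 carried; −50 − 15 = −65 poor score.
- NIHSS: 0 + 3 = 3 carried; 30 + 3 = 33 poor score.

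| Mortality A v B (dB − dA) | Survivors only | VAS carried | VAS poor score | NIHSS carried | NIHSS poor score |
|---|---|---|---|---|---|
| 1% v 3% (0.02) | 0 | −0.30 | −1.30 | +0.06 | +0.66 |
| 2% v 5% (0.03) | 0 | −0.45 | −1.95 | +0.09 | +0.99 |
| 2% v 10% (0.08) | 0 | −1.20 | −5.20 | +0.24 | +2.64 |

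Carrying forward keeps 15/65 = 23% of the contrast for VAS and 3/33 = 9% for NIHSS. The survivors-only comparison keeps none.

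For deaths after Visit 2, suppose instead that the carried NIHSS is 2 points above baseline and survivors change by −2. At 2% v 5% the difference is 0.03 × (2 + 2) = 0.12 points.

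In these examples the difference in means shrinks or vanishes; it does not change sign.

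**The case against.** The strongest reply is that deaths are not hidden from the study. Death counts against a regimen in the primary endpoint, and the 90-day death proportion is compared between groups in a secondary endpoint. The study is also a non-interventional registry whose primary objective is descriptive. This stands, and it confines the point to two secondary endpoints. It does not repair their ordering of outcomes.

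A second reply is that handling of death belongs in the statistical analysis plan, which is not shown and may contain an exception. That would be an answer if the protocol were silent. It is not: section 10 names the method for absent efficacy scores, applies it if needed, and makes no exception.

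Third, ranking deaths last in an unadjusted comparison also counts against a regimen given to sicker patients. This is true, and the fix does not remove it.

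Three stronger readings are tempting, and the documents do not support them:

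- *QALYs are overstated for the more lethal regimen.* Section 8.3 builds the path by "connecting the utility values on day 0, at discharge, on 90 ± 14 days after medication", and the tariff has no entry for death. But that section defers the calculation to a cited source not at hand, section 1 says QALYs reflect life-span, the date of death is collected, and section 10 limits carrying forward to efficacy. Nor is the direction fixed. Taking utility as 1 minus the constant and the decrements, the worst state is 1 − 0.152 − (0.418 + 0.102 + 0.133 + 0.194 + 0.112) = −0.111, and carrying that forward would lower QALYs.
- *In-hospital mortality will differ between regimens.* The protocol gives no mortality figure. A difference is plausible, not established.
- *Scoring death at the worst scale value is the same as ranking it last.* It is not, for a change score. With an NIHSS maximum of 42, a death from baseline 36 has change +6 and ranks better than a survivor who worsened by 8. Nor is 42 stated: Annex 1 prints one arm and one leg row, and its row maxima sum to 34.

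**Conclusion.** The point holds for change to discharge in NIHSS and EQ-5D VAS. If the carrying-forward rule is applied as written, an in-hospital death becomes a VAS change of exactly 0, and an NIHSS change of 0 or the last living value, unless an early death leaves the full analysis set. Such a patient can rank better than a survivor who worsens. If the rule is not applied, only survivors are compared.

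The misordering follows from the stated rules and the visit schedule. The size does not: it depends on mortality and score changes that the documents do not give, and the 23% and 9% rest on the assumed values shown. The primary endpoint and the 90-day death proportion stand, because mRS 6 gives death a value. No conclusion is drawn about the QALY analysis.

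**What to change.** - **Section 10:** state that carrying forward does not apply to scores absent because of death.
- **Section 10.3:** for these two endpoints, make the rank-based branch already planned (Kruskal-Wallis, then Wilcoxon with Bonferroni) the analysis. Rank patients who die before the discharge assessment below all survivors. Include those who die before Visit 2, and say so against the section 10.2 definition so that the post-baseline requirement does not remove them.
- **Reporting:** show survivors' change descriptively beside the test, with the number of deaths before discharge in each regimen.

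The cost is wording in the protocol and analysis plan. No new data are needed, since survival status and date of death are already collected. The downsides are that each result becomes a composite of death and score change, which is why survivors' change is shown beside it, and that, like the other unadjusted comparisons, it still reflects differences in baseline severity between regimens.
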